## Abstract

**Background:**

The number of elective outpatient surgeries in Canada has increased markedly in the last 10 years. However, unanticipated cancellations on the day of surgery and adverse postoperative events are frequent. Modern technologies have been shown to be of great help in the medical field in improving patient care. Thus, it is likely that dedicated technologies could also significantly improve surgical outpatients’ pathways. Therefore, the department of anesthesiology at the University of Montreal Medical Center, in collaboration with LeoMed, a telemedicine platform, has developed a telehealth solution to offer more efficient perioperative support and follow-up for patients undergoing ambulatory surgery.

**Objective:**

The objective is to evaluate the medicoeconomic benefit of a dedicated perioperative telehealth platform for patients undergoing day surgery. Our hypothesis is that this dedicated telecare solution will allow more efficient patient care, which will reduce all types of medical costs related to day surgery pathways.

**Methods:**

This study is a single-center, single-blinded, 2-group randomized controlled trial. One thousand patients aged over 18 years with internet access who are scheduled to undergo ambulatory surgery will be enrolled and randomized either to follow a perioperative path that includes a patient-tailored perioperative digital app via the LeoMed telecare platform for 1 month or to follow the standard of care, which does not offer personalized digital support. The primary outcome will be to evaluate the cost-effectiveness of the telecare platform, assessing direct costs from factors such as unanticipated cancellations on the day of surgery due to preoperative instructions not being followed, calls to the local health information line, calls to the provincial health information line, emergency department consultations, unplanned readmissions, or medical visits for problems related to the surgical procedure within the first 30 days after the intervention. The secondary outcome will be to evaluate cost utility using a questionnaire assessing quality-adjusted life years. A blinded independent research team will analyze outcomes. All data will be analyzed according to the intention-to-treat principle. A sample size of 500 subjects in each group was calculated to detect a 21% reduction in postoperative complications with a power of 90%. This study has been approved by the ethics board of Centre hospitalier de l’Université de Montréal (University of Montreal Health Centre). No employee of LeoMed was involved in the study conception, and none will be involved in either data collection or analysis.

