## Introduction

Outpatient surgeries have increased significantly in the last 3 decades [1]. In Canada, there was an overall 30% increase in outpatient surgeries between the fiscal years 1995-1996 and 2005-2006 [2]. In some countries, day surgeries account for more than 70% of all elective procedures [3]. Nowadays, it is common to perform day surgeries for both higher-risk patients and procedures [4]. However, postoperative measures currently in place to support and follow patients undergoing day surgeries are suboptimal. Indeed, a recent Canadian study has shown that the same-day cancellation rate for outpatient surgeries ranges from 8% to 10% [5,6]. The authors of that study also mentioned that 60% of these cancellations could have been avoided with better preoperative support [7]. Despite current recommendations, adverse postoperative events are very rarely searched for or detected by health care institutions [8-10]. The most common reasons for readmission, emergency department consultation, or unplanned medical visits are postoperative pain, nausea, and vomiting [10]. In addition, the prevalence of moderate-to-severe postoperative pain after ambulatory surgery ranges from 21% to 30% at 24 hours, and as much as 24% to 43% at 7 days [11,12]. This could lead to inappropriate postoperative use of opioids [13]. Inadequate pain relief is also one of the main risk factors for impairment of patients’ overall quality of life after surgery [14]. A recent report by the Canadian Institute for Health Information showed that patients scheduled for day surgery in Canadian teaching hospitals return to the emergency department or are readmitted within 30 days postoperatively at incidence rates of 9.4% and 7.3%, respectively [15]. The additional costs associated with these cancellations and unplanned readmissions amount to several billion dollars every year [15].

In efforts to ensure better perioperative support and follow-up for patients undergoing day surgeries, many tools have been developed [16]. With recent technological advances and with the widespread use of smartphones and tablets, digital solutions have been suggested to guide and follow these patients [17].

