### Blinding and Allocation Concealment

Eligible patients will first be approached by telephone by a member of the research team when the preoperative clinical appointment is booked. During the preoperative clinical assessment, patients will receive both oral and written information on the study by a research nurse not involved in patient care. Patients will be included in the trial only after a research nurse has obtained written informed consent.

All included patients will be electronically randomized into the intervention group or the control group. Randomization will be performed by one of the investigators using the MedSharing Randomizer for Clinical Trial web application. The 2 groups will be balanced at a 1:1 ratio. Patients who are recruited but do not receive surgery within the study time frame will be secondarily excluded.

The study will be single-blinded. Statisticians will assess the primary and secondary outcomes, blinded to the randomization group. However, due to the nature of the intervention, neither the patients nor the care providers will be blinded to the randomization.

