### Sample Size

There are very few studies that have examined the effects of digital solutions for personalized support and follow-up for patients undergoing day surgery. We based our sample size calculations on Jaensson et al [25], assuming that a better postoperative recovery (ie, decreased symptoms and complications) should reduce the number of postoperative calls to the health information line, visits to the emergency department, unplanned readmissions and medical visits, and the associated costs (our primary outcome). Jaensson et al [25] reported better recovery (based on the global Swedish Web Version of the Quality of Recovery [SwQoR] score) in an intervention group (ie, day surgery patients using a recovery assessment mobile phone app) compared with a control group (standard care) on POD 7 (effect size 0.21; *P*<.001). With a significance level of .05 and a statistical power of .90, G*Power (Heinrich Heine University) generated a group size of 357. To allow for a 20% rate of loss to follow-up and protocol deviations, we thus aim to recruit 500 patients per arm. In the third quarter of 2019, CHUM provided nearly 630 outpatient surgical stays per month on average. Considering 70% of patients should be eligible for the study [26], it will take about 12 months to recruit 1000 patients.

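### The abstract's 90% power for a 21% fall in complications restates a standardised effect of 0.21 on a recovery score, and even for that score 357 per group gives 80% power, not 90%

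*Protocol article*

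**What the plan says.** The abstract (Methods) makes one power statement: "A sample size of 500 subjects in each group was calculated to detect a 21% reduction in postoperative complications with a power of 90"%.

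The Sample Size section describes a different calculation. The cited trial "reported better recovery (based on the global Swedish Web Version of the Quality of Recovery [SwQoR] score) in an intervention group", that is, in day surgery patients using a recovery app, "compared with a control group (standard care) on POD 7 (effect size 0.21"). The section then reports: "With a significance level of .05 and a statistical power of .90, G*Power (Heinrich Heine University) generated a group size of 357". It continues: "To allow for a 20% rate of loss to follow-up and protocol deviations, we thus aim to recruit 500 patients per arm". The link to this trial's outcome is stated as an assumption: better recovery should lower calls, visits, readmissions and their costs.

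The primary outcome is cost-effectiveness through direct costs, built from six kinds of event: cancellations due to unfollowed instructions, calls to the hospital line, calls to the provincial line, emergency visits, unplanned readmissions and unplanned medical visits. The secondary outcome is QALYs, and patient satisfaction is also assessed. Neither a complication rate nor the SwQoR appears among the outcomes or in Table 1. The only 30-day rates given for any component are in the Introduction: patients "return to the emergency department or are readmitted within 30 days postoperatively at incidence rates of 9.4% and 7.3%, respectively".

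**The concern.** A standardised difference of 0.21 is a shift of about a fifth of a standard deviation in a continuous score. It is not a 21% reduction in anything, and it says nothing about the frequency of an event. The abstract changes both the unit (0.21 becomes 21%) and the endpoint (a recovery score becomes complications), and attaches 90% power to the result.

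The abstract is the part most people read. Someone relying on it would think the trial well placed to detect a modest fall in complications, and could take a null finding on emergency visits or readmissions as evidence that the platform does not help. The Discussion presents the trial as evidence for government and public insurers, so that misreading would matter.

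**Working it through.** **Inputs.** Effect size 0.21, alpha .05, power .90, 357 per group, 20% loss and 500 recruited per arm (Sample Size); 1:1 allocation (Blinding and Allocation Concealment); emergency return 9.4% and readmission 7.3% (Introduction). The sidedness of the test is not stated; I take two-sided. With the planned loss, 500 × 0.80 = 400 per arm are analysed.

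**1. The plan's own figure.** For a difference d in standard deviation units, n per group = 2(z₁₋α/₂ + z₁₋β)² / d².
- 90% power: 2 × (1.960 + 1.282)² / 0.21² = 476.5, so 477 (478 by the exact t test).
- 80% power: 2 × (1.960 + 0.842)² / 0.21² = 356.0 (357 by the exact t test).
- One-sided: 281 for 80%, 389 for 90%.

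The stated 357 is exactly the two-sided t-test answer for d = 0.21 at 80% power. This shows that 0.21 was entered as a standardised difference, and that the accompanying .90 is wrong.

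**2. Power for d = 0.21 at the planned sizes.** Power = Φ(0.21 × √(n/2) − 1.960).
- n = 357: Φ(2.806 − 1.960) = 80%.
- n = 400: Φ(2.970 − 1.960) = 84%.
- n = 500: Φ(3.320 − 1.960) = 91%.

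The allowance for loss does not lead to 500 either: 357 / 0.80 = 446.25, so 447. Starting from 478, 478 / 0.80 = 597.5, so 598.

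**3. Power for a 21% relative cut in events.** Two-proportion z test, p₂ = 0.79 p₁, power = Φ((p₁ − p₂ − 1.960 × SE₀) / SE₁), with SE₀ pooled and SE₁ unpooled. Example at p₁ = .094, n = 400: p₂ = .0743, SE₀ = .01963, SE₁ = .01962; (.01974 − .03847) / .01962 = −0.955, so power is 17.0%.

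| Control rate | After a 21% cut | Power, 400 per arm | Power, 500 per arm | n per arm for 90% |
|---|---|---|---|---|
| Readmission 7.3% | 5.8% | 13.9% | 16.4% | 5459 |
| Emergency return 9.4% | 7.4% | 17.0% | 20.2% | 4154 |
| Sum 16.7% (no overlap assumed) | 13.2% | 28.4% | 34.3% | 2171 |

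The Introduction also gives an all-cause "same-day cancellation rate for outpatient surgeries ranges from 8% to 10"%; a 21% cut there has 15–21% power.

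**4. Control rate at which the abstract's sentence would be true.** Power for a 21% relative cut reaches 90% at a control rate of 48.3% with 500 per arm and 54.4% with 400. The highest adverse-event rate quoted is 43% (moderate-to-severe pain at 7 days, not a component of the primary outcome), which gives 75–84%.

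**5. What 400 to 500 per arm can detect with 90% power.** A relative reduction of about 60% to 55% from 9.4%, or about 67% to 61% from 7.3%.

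**The case against.** The strongest reply is that the event calculations cover only part of what the trial counts. Emergency return and readmission are two of six components, and their rates are national teaching-hospital figures. A reader might infer that power for the trial's own events is 14–34%. The documents do not support that: they give no rate for calls, medical visits or the composite, so 34% is not an upper bound. A 20% control rate would give 34–41% and a 30% rate 52–61%. If events were analysed as counts with, as a pure assumption, one Poisson event per control patient, a 21% reduction would have about 88–94% power. This stands, and it limits the event figures to the two quoted rates. It does not rescue the abstract, which claims a calculation for complications that was not made.

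A second tempting inference is that power for costs is equally low. No cost mean, standard deviation or coefficient of variation appears anywhere, so any such figure would be illustrative only.

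Third, the Methods disclose that a recovery score from another trial serves as a proxy. That is fair: using a proxy is not the error. The error lies in the abstract's restatement and in the power attached to 357.

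Fourth, a one-sided test would raise the event figures to 22–46%. At the 43% pain rate with no loss it would just reach 90%. But 357 matches the two-sided calculation, not a one-sided one at 80% or 90%.

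Finally, no significance test is named for emergency visits, readmissions or costs, so the risk of misreading a null result is a risk for readers, not a flaw in a stated analysis.

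**Conclusion.** The concern holds. The abstract's power statement contradicts the Sample Size section and is wrong as written: the trial was sized on a standardised difference of 0.21 in a score it does not list as an outcome, and the 90% carries over neither to complications nor to the primary outcome. Power for complications cannot be computed, because no complication rate is given. For the two 30-day components with quoted rates, the chance of detecting a 21% cut runs from about one in seven (readmission, 400 per arm) to one in five (emergency return, 500 per arm), and to about one in three if the two are summed without overlap. No adverse-event rate in the document brings a two-sided test to 90%.

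The stated power is also wrong for the score itself. It is 80% at the calculated 357 and about 84% if the planned 20% loss occurs; only with all 500 per arm analysed does it exceed 90%, at about 91%. These results assume a two-sided .05 test and equal arms. They do not show that the trial is too small for its full composite or for costs.

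**What to change.** 1. In the abstract, replace the sentence on a 21% reduction in complications. State that the calculation was for a standardised difference of 0.21 in a recovery score from a cited trial, used as a proxy, and that no power is claimed for complications or costs.
2. Correct the power in both the abstract and the Sample Size section, and state the sidedness: 357 per group gives 80% two-sided, 90% needs 478, and 500 recruited gives about 91% with no loss and about 84% after 20% loss.
3. Optionally, add what 400 to 500 per arm can detect with 90% power at the quoted rates: about a 55–60% relative reduction in emergency visits, or 61–67% in readmissions. Any cost figure based on an assumed coefficient of variation should be left out or labelled illustrative.

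The cost is a few sentences. Recruitment, outcomes and analysis do not change, but the stated power becomes less favourable.

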**Results:**

Results of this trial will be useful to determine the economic benefit of a telecare platform specifically developed for surgical outpatient pathways.

**Conclusions:**

We believe that the deployment of a dedicated perioperative telehealth app will lead to better patient care and fewer postoperative complications, which will lower all types of costs related to surgical outpatient care.

**Trial Registration:**

ClinicalTrials.gov NCT04948632; https://ClinicalTrials.gov/ct2/show/NCT04948632

**International Registered Report Identifier (IRRID):**

DERR1-10.2196/44006

## Introduction

Outpatient surgeries have increased significantly in the last 3 decades [1]. In Canada, there was an overall 30% increase in outpatient surgeries between the fiscal years 1995-1996 and 2005-2006 [2]. In some countries, day surgeries account for more than 70% of all elective procedures [3]. Nowadays, it is common to perform day surgeries for both higher-risk patients and procedures [4]. However, postoperative measures currently in place to support and follow patients undergoing day surgeries are suboptimal. Indeed, a recent Canadian study has shown that the same-day cancellation rate for outpatient surgeries ranges from 8% to 10% [5,6]. The authors of that study also mentioned that 60% of these cancellations could have been avoided with better preoperative support [7]. Despite current recommendations, adverse postoperative events are very rarely searched for or detected by health care institutions [8-10]. The most common reasons for readmission, emergency department consultation, or unplanned medical visits are postoperative pain, nausea, and vomiting [10]. In addition, the prevalence of moderate-to-severe postoperative pain after ambulatory surgery ranges from 21% to 30% at 24 hours, and as much as 24% to 43% at 7 days [11,12]. This could lead to inappropriate postoperative use of opioids [13]. Inadequate pain relief is also one of the main risk factors for impairment of patients’ overall quality of life after surgery [14]. A recent report by the Canadian Institute for Health Information showed that patients scheduled for day surgery in Canadian teaching hospitals return to the emergency department or are readmitted within 30 days postoperatively at incidence rates of 9.4% and 7.3%, respectively [15]. The additional costs associated with these cancellations and unplanned readmissions amount to several billion dollars every year [15].

In efforts to ensure better perioperative support and follow-up for patients undergoing day surgeries, many tools have been developed [16]. With recent technological advances and with the widespread use of smartphones and tablets, digital solutions have been suggested to guide and follow these patients [17].

The department of anesthesiology at the Centre hospitalier de l’Université de Montréal (CHUM; University of Montreal Medical Center in English), in collaboration with LeoMed, has developed a dedicated digital smart solution specifically designed to offer personalized perioperative support and follow-up via a telecare platform that can easily be installed on any smartphone. We hypothesize that the implementation of this telehealth platform at CHUM will (1) reduce the rate of unanticipated cancellations of elective surgeries through better preoperative information and communication, (2) improve quality of life 30 days after surgery due to faster and better recognition of postoperative complications, and (3) reduce the rate of emergency department or unplanned medical visits and unnecessary calls to the health information line, as well as reduce unplanned hospital readmissions, through more personalized health support. Our overall conjecture is that including the LeoMed patient-tailored telecare platform in the perioperative day-surgery pathways of patients will improve the medicoeconomic impact of care services compared with standard care. The main objective of this study is to assess the cost-effectiveness of the LeoMed platform, and our secondary objective is to perform a cost-utility analysis.

## Methods

### Design

In order to achieve the abovementioned objectives, we propose to conduct a single-center, single-blinded, 2-group randomized controlled trial. A group of patients who use the LeoMed patient-tailored telecare platform will be compared to a group of patients who have access to usual care. As mentioned earlier, the study will be conducted at CHUM.

### Population

All patients aged over 18 years who undergo elective day surgery under general or regional anesthesia at CHUM will be eligible. All included patients must (1) have internet access and (2) understand written and oral French or English. Patients were possibly excluded at two stages: (1) before randomization, if they were unable to learn and use the digital technologies or if they refused to participate, and (2) after randomization, in cases of conversions from outpatient to inpatient hospitalization on the day of surgery or in cases of last-minute postponement of the surgery to a later date. Figure 1 shows the trial flowchart.

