### Primary Outcome

The primary outcome will be the cost-effectiveness of the LeoMed telecare platform deployment assessed by its direct costs, including unanticipated cancellations on the day of surgery due to preoperative instructions not being followed, calls to the local CHUM health information line, calls to the Quebec health information line (ie, 811), visits to the emergency department, and unplanned readmissions or medical visits (to family doctors or outpatient clinics) for problems related to the procedure within the first 30 days after the procedure.

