### Data Collection

Data for primary and some secondary outcome measures will be collected from the LeoMed platform until POD 30, with the exception of same-day cancellations. These data will be collected on POD 1 from the electronic medical record (EMR) system by 1 member of the research team (Table 1). In the absence of spontaneous responses from patients at POD 30 or if the forms are incomplete, patients will be called by one of the research assistants to assess the indicators included in the cost-effectiveness and cost-utility analyses. If a postoperative event is reported via the form, the patient will also be contacted personally by telephone.

For each patient, data will be systematically registered and archived on a local secure server. Patients will be identified using a unique numeric code, and all patient data will be anonymized to ensure confidentiality. All data will be extracted and cross-referenced with Oacis (Telus Health), the EMR system used at CHUM.

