### Data Analysis

Data analysis will be performed by a team of researchers at the École des Hautes Études Commerciales in Montreal, Quebec, using SPSS (version 28; IBM Corp). All data will be analyzed according to the intention-to-treat principle. Descriptive statistics will be reported as frequencies and proportions for categorical data and means and standard deviations for continuous variables. Demographic data for the 2 groups of patients will be compared using the Mann-Whitney *U* test (for ordinal data), the chi-square test (for nominal data), and a 2-tailed *t* test (for continuous data).

Considering the Canadian guidelines for the economic evaluation of health technologies [22], the perspective of the health care system will be privileged in this study. Specifically, 2 main types of analyses will be carried out. First, all interventions in both groups related to surgery (calls to the provincial or CHUM information lines, visits to the ambulatory unit, hospital readmissions, and visits to the emergency department) will be recorded during the study to perform the cost-effectiveness analysis. Second, a cost-utility analysis will be conducted to quality-weight each effectiveness outcome measured in QALYs. QALYs will be calculated as life with the health state under study multiplied by the utility associated with that health state. CHUM’s internal data will be used to determine the cost of health care staff and the average cost of an emergency room visit for the clientele concerned in fiscal year 2019-2020. For hospitalizations, we will use the average costs calculated according to the American diagnosis-related groups method, which was applied at CHUM in 2019-2020. Technology costs will be estimated based on license prices in effect at the time of the study and amortized on a straight-line basis over a 5-year period. All calculations will be in Canadian dollars. Last, patient satisfaction with care services will be measured in both groups at the end of the trial using Likert scales adapted from Sicotte et al [23]. This protocol follows the SPIRIT (Standard Protocol Items: Recommendation for Interventional Trials) 2013 Statement for trial protocols [24].

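### Excluding allocated patients for last-minute postponement or same-day inpatient conversion contradicts intention-to-treat and can remove, unequally by arm, some of the cancellations the primary outcome counts

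*Protocol article*

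**What the plan says.** Two places in the protocol article remove patients after they have entered the trial.

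- **Population:** exclusion is possible "after randomization, in cases of conversions from outpatient to inpatient hospitalization on the day of surgery or in cases of last-minute postponement" of the operation.
- **Blinding and Allocation Concealment:** "Patients who are recruited but do not receive surgery within the study time frame will be secondarily excluded".

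Four other statements bear on these rules.

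- **Data Analysis** (and the Abstract): "All data will be analyzed according to the intention-to-treat principle".
- **Primary Outcome:** the direct costs are described as "including unanticipated cancellations on the day of surgery due to preoperative instructions not being followed", followed by calls, visits and readmissions.
- **Introduction:** the first hypothesis is that the platform will "reduce the rate of unanticipated cancellations of elective surgeries through better preoperative information and communication".
- **Data Collection**, on same-day cancellations: "These data will be collected on POD 1 from the electronic medical record (EMR) system by 1 member of the research team".

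On timing, Recruitment and Intervention and Table 1 place allocation at confirmation of the surgery date. The Intervention Group section places the preoperative message on the day before surgery. Patients and care providers are not blinded.

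**The concern.** An intention-to-treat analysis keeps each randomised patient in the assigned arm whatever happens next. Postponement and conversion both happen after allocation and after the preoperative part of the intervention has been delivered. Dropping patients on those grounds is incompatible with the stated principle.

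The conflict reaches the primary outcome. A patient sent home on the day of surgery for not following instructions may be given a later date. On a plain reading, that patient has both a countable cancellation and a reason for exclusion. The article does not say which prevails.

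Two things are at stake. Part of the cancellation cost may vanish from the comparison. Also, if the platform works as hypothesised, the control arm loses more patients than the intervention arm, and those lost are the less adherent ones. The retained groups are then no longer the randomised groups. Blinding the statisticians cannot repair a selection that happened before the data reached them.

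**Working it through.** **Step 1: set the rules side by side.**

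| Event after allocation | Exclusion rule | Listed in the primary outcome? | Hypothesised effect of the platform? |
|---|---|---|---|
| Same-day cancellation, instructions not followed, new date given | Population, if treated as a last-minute postponement | Yes | Yes |
| Same-day cancellation, instructions not followed, no surgery in the time frame | Blinding and Allocation Concealment | Yes | Yes |
| Last-minute postponement for another reason | Population | No | Not necessarily |
| Same-day conversion to inpatient stay | Population | No | No |

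All four rows conflict with intention-to-treat. Only the first two can remove events that the primary outcome counts. Nothing in the article says that a cancellation is recorded before the patient is removed.

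**Step 2: inputs for an upper illustration.** The article gives no expected number of cancellations for this trial, so there is no planned figure to reproduce.

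- Same-day cancellation rate, Introduction: "the same-day cancellation rate for outpatient surgeries ranges from 8% to 10" per cent.
- Share avoidable with better preoperative support, Introduction: 60%.
- Patients per arm, Sample Size: 500.

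**Step 3: expected events without any platform effect.**

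- Cancellations per arm = 500 × rate: 500 × 0.08 = 40; 500 × 0.10 = 50. Over both arms: 80 to 100.
- Avoidable per arm = cancellations × 0.60: 40 × 0.60 = 24; 50 × 0.60 = 30. Over both arms: 48 to 60.

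**Step 4: what exclusion could hide.** Assume, for illustration only, that every same-day cancellation leads to exclusion and that the platform prevents a fraction *f* of the avoidable ones. Cancellations in the intervention arm are then 500 × rate × (1 − 0.60 × *f*).

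| Rate | *f* | Control cancelled | Intervention cancelled | Difference not seen | Retained, control / intervention |
|---|---|---|---|---|---|
| 8% | 0.5 | 40 | 28 | 12 | 460 / 472 |
| 8% | 1 | 40 | 16 | 24 | 460 / 484 |
| 10% | 0.5 | 50 | 35 | 15 | 450 / 465 |
| 10% | 1 | 50 | 20 | 30 | 450 / 480 |

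Under these assumptions, 12 to 30 fewer cancellations per 500 would be invisible, and the arms would be selected unequally by the same number of patients.

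**The case against.** The strongest reply is that a reader might infer too much: that the cancellation component is close to zero by design, that the first hypothesis cannot be tested, and that 24 to 30 counted events per arm will be deleted. The documents do not support any of these.

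- **The terms differ.** The outcome is defined by cause, "unanticipated cancellations on the day of surgery due to preoperative instructions not being followed"; the exclusion names no cause. The Discussion says the operating program is confirmed only the day before surgery, so last-minute postponement could mean institutional rescheduling. That a cancelled patient is normally rebooked is an assumption.
- **The authors evidently meant to count cancellations.** These have their own route through the EMR. Exclusion could mean removal from postoperative follow-up only.
- **The figures are loose.** Avoidable with better support is not the same as instructions not followed, and no rate is given for the latter. The 8% to 10% comes from cited work, not from this trial's patients.
- **The second exclusion is narrower than it looks.** It does not remove everyone whose operation is cancelled. A patient operated on later within the time frame is not caught, and some recruited patients may never have been allocated.
- **Conversion is a weaker limb.** It is neither a listed component nor part of a hypothesis.
- **Exclusion is described as possible**, and Sample Size allows 20% for loss to follow-up and protocol deviations.

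All of this limits the size of the problem and stands to that extent. It does not remove the conflict. No section says that a postponed patient's cancellation is kept. Discretionary exclusion in an unblinded trial is no safer than a fixed rule. A recruitment allowance protects precision, not comparability. Nor is this a detail left to an analysis plan: the article itself states both incompatible rules.

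**Conclusion.** The point holds in a bounded form. For allocated patients, the exclusions in Population and in Blinding and Allocation Concealment contradict the intention-to-treat statement. Because same-day cancellation is both a primary cost component and an expected effect of the platform, and is not separated from last-minute postponement, the rule can delete an unknown share of those events and can do so unequally by arm.

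The size cannot be fixed from the article. The 40 to 50 cancellations per arm, 24 to 30 of them avoidable, are an upper illustration. They assume that the Introduction's rates apply here, that avoidable cancellations are instruction-related, and that such cancellations are handled as excluded postponements. Excluding conversions breaks intention-to-treat and omits a cost relevant to the health care system perspective, but deletes no cancellation.

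This should be corrected because it touches the primary outcome and the integrity of the randomised comparison, whatever the true overlap.

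**What to change.** Reconcile Population, Blinding and Allocation Concealment, Primary Outcome and Data Analysis as follows.

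1. Analyse every allocated patient in the assigned arm. Limit exclusion to patients never allocated.
2. Count and cost each same-day cancellation that meets the primary-outcome definition, from the EMR, whether or not surgery is later rescheduled. State how it relates to a last-minute postponement.
3. Include the cost of same-day inpatient conversions.
4. For patients operated on later, keep the 30-day window from the actual procedure, as Primary Outcome requires. For allocated patients never operated on, count the cancellation and other costs over a prespecified window from the scheduled date.
5. Report the operated-as-day-case set as a sensitivity analysis only.

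Starting the window at the scheduled date for everyone would be simpler but is not advised. A patient postponed by 21 days would have only 30 − 21 = 9 postoperative days observed.

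The cost is a wording change plus POD 15 and POD 30 forms for a small number of additional patients. Cancellations already come from the EMR, and the stated sample size need not change on this account. The article reports 142 of the planned 1000 patients enrolled by October 31, 2022. Allocated patients already excluded should be restored to their arms, with their cancellations taken from the EMR.
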